#### Follow-up

The trial design will allow the comparative evaluation of both the conventional mammogram and MammoWave’s AI solution in terms of cancer detection rate, the number of recalls and positive predictive value, having as reference standard the 2-year follow-up of each volunteer. This follow-up allows to check retrospectively the possible rate of interval BC, and if this was reported as a false positive by MammoWave.

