**Trial registration number:**

NCT06291896.

STRENGTHS AND LIMITATIONS OF THIS STUDYThis is the first multicentric, prospective study to evaluate the sensitivity and specificity of MammoWave’s artificial intelligence (AI) solution within the framework of an asymptomatic population-based programme for breast cancer detection.The MammoWave device will use an AI-powered clinical decision support system to automatically provide radiologists with a dedicated label indicating the presence or absence of suspicious findings in each breast.As a reference standard, the 2-year follow-up with histological confirmation of cancer cases will be used.Study limitations include its non-randomised design.The axillary region of the breast is not captured within MammoWave’s cup.

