#### Hypothesis and objectives

The aim of this clinical study is to validate, prospectively, MammoWave’s AI-based classification algorithm. The hypothesis underlying this clinical study is that MammoWave’s AI-based classification algorithm achieves a sensitivity of over 75% and a specificity of over 90% in the detection of BC within the screening process of asymptomatic individuals currently enrolled in population-based screening programmes.

The primary objective of this study is to generate evidence in the detection of BC by using MammoWave, evaluating its sensitivity and specificity, having as reference standard the output of conventional breast examination path (ie, screening mammogram, integrated with other radiological/histological output when deemed necessary by the responsible Investigator).

The secondary objectives of the study are as follows:

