Evaluation of the sensitivity of MammoWave in detecting BC according to the American College of Radiology (ACR) BI-RADS classification.^37^Evaluation of the effectiveness of MammoWave versus a conventional reading of digital mammographic images (either 2D or tomosynthesis) and analysis of whether they are equivalent in terms of detection rates of BC (sensitivity),the number of recalls and positive predictive value (for the biopsies performed).Evaluation of the detection rate (sensitivity) of each system according to the type of mammographic radiological finding (microcalcification, mass, asymmetry or architectural distortion group).Evaluation of the impact of breast density (according to the ACR BI-RADS classification^37^ assigned by the radiologist, with or without automatic software if available) on the MammoWave detection rate of BC, number of recalls and positive predictive value (of the biopsies performed).Evaluation of the impact of breast density (according to BI-RADS classification assigned by the radiologist^37^) on the detection rate (sensitivity) of each system depending on the type of finding (microcalcification, mass, asymmetry or architectural distortion group).Comparison of radiological, histological and stage characteristics between the BCs detected by each system.Evaluation of the reproducibility of the AI-based MammoWave software’s results.Evaluation of the improvement in both sensitivity and specificity when retrospectively using AI algorithms to evaluate MammoWave data after its further optimisation with all the data collected in the patients included in the study.Volunteers’ satisfaction related to MammoWave use, through a properly designed questionnaire (given here as online supplemental material), collecting women’s issues during the exam with MammoWave in the language spoken by the women.

Additionally, there is a secondary objective, which is related to MammoWave safety and tolerability assessment. Furthermore, an additional exploratory objective of the clinical study is to establish a predictive model capable of discriminating and classifying lesions in MammoWave outcomes for volunteers with breast lesions, if feasible.

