#### Study period

Recruitment started in February 2024; recruitment of the last participant is planned for February 2026. The deadline for the first evaluation of the results is planned for December 2026.

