#### Choice of comparator/control intervention

MammoWave’s results (labels provided by its AI-based classification algorithm) will undergo validation against a reference standard, which represents the output of the conventional breast examination pathway. This pathway includes screening mammograms conducted with DM or DBT, integrated with other radiological/histological findings as required by the responsible investigator, following the site’s ongoing procedures and clinical circuit. The reference standard’s results will be categorised as ‘positive’ when BC presence is confirmed by histology (ie, BI-RADS 6), otherwise labelled as ‘negative’ (BI-RADS 1, 2 or 3). Specifically, within this study BI-RADS 4 and BI-RADS 5 are only image suspicion criteria: when a biopsy is performed, they will be categorised as ‘positive’ when BC presence is confirmed by histology (ie, BI-RADS 6), otherwise labelled as ‘negative’ (BI-RADS 1, 2 or 3).

Conventional mammogram studies (2D or tomosynthesis) will adhere to approved protocols and clinical practices for breast screening. Radiological reports and interpretations will align with international guidelines, particularly those set by the ACR.^37^ The radiologists involved in this study will have extensive experience in mammographic interpretation, serving as the benchmark during the study. Details such as single or double screening readings and the utilisation of AI-assisted mammographic reading will be documented at each centre. Additionally, the integration of conventional mammogram studies with other radiological/histological findings will occur when deemed necessary by responsible investigators, who will record relevant variables in the electronic case report form (eCRF) following their usual clinical practice.

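### The reference standard for primary sensitivity and specificity is the index diagnostic pathway in some sections and 2-year follow-up in others, and the December 2026 evaluation comes before 2-year follow-up is complete

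*Protocol article*

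**What the plan says.** All references are to the Protocol article.

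**Index pathway only.** Under Hypothesis and objectives, the primary objective evaluates sensitivity and specificity "having as reference standard the output of conventional breast examination path (ie, screening mammogram, integrated with other radiological/histological output when deemed necessary". Choice of comparator/control intervention validates the labels against a reference standard "which represents the output of the conventional breast examination pathway". It then gives the coding rule: positive if histology confirms cancer, "otherwise labelled as ‘negative’ (BI-RADS 1, 2 or 3"). Neither section mentions follow-up.

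**Two-year follow-up.** The strengths and limitations box, printed under the trial registration number, says: "As a reference standard, the 2-year follow-up with histological confirmation of cancer cases will be used". The abstract defines the standard as the conventional pathway with histological confirmation together with 2 years of follow-up. The Follow-up section describes the comparison of mammography and MammoWave "having as reference standard the 2-year follow-up of each volunteer". Its next sentence says that follow-up allows a retrospective check on interval cancers and on whether MammoWave had reported them as false positives.

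**Dates.** Study period places recruitment from February 2024 to February 2026, and adds: "The deadline for the first evaluation of the results is planned for December 2026".

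**Sample size.** Number of participants uses a screen-detected prevalence of 0.92% and states a minimum of 8000 participants, with a maximum of 10 000.

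**The concern.** The two definitions classify the same woman in opposite ways. If her index work-up is clear and cancer appears within 2 years, the coding rule leaves her negative, so a MammoWave flag counts as a false positive and a missed flag as a true negative. Under the 2-year definition the same results are a true positive and a false negative. The Follow-up section itself mixes the two: it names 2-year follow-up as the standard and then calls a flagged interval cancer a false positive, a description that fits only the index definition.

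The article does not say which definition governs the primary endpoint. In the second phase, women negative on both tests have no further examination specified by the study, so the index definition counts cancers missed by both as true negatives. Unless the choice is fixed beforehand, it could be made after the data are seen. The December 2026 evaluation has the same gap: the article does not say which standard it uses, and most women may not yet have 2 years of follow-up.

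**Working it through.** **1. Reproducing the plan's sample size.** Inputs from Number of participants: sensitivity 0.75, 95% two-sided interval, 10 points, prevalence 0.0092. With the 10 points taken as the half-width:
- Cancers needed: 1.96² × 0.75 × 0.25 / 0.10² = 72.03.
- Women needed: 72.03 / 0.0092, rounded up, is 7830; rounding to 73 cancers first gives 7935.

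Both agree with the stated 8000. (As a full width, the 10 points would give 31 317.) The prevalence is that of screen-detected cancer, so the calculation includes no interval cancers and matches the index definition.

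**2. Follow-up complete at December 2026.** Only women enrolled by December 2024 can have 2 years. With even accrual over 24 months (assumption):
- Share complete: 10/24 = 41.7% to 11/24 = 45.8%, or about 4170 to 4580 of 10 000 women.
- Screen-detected cancers among them: × 0.0092 = about 38 to 42, against about 72 in step 1.
- Half-width at 38.3 cancers: 1.96 × √(0.75 × 0.25 / 38.3) = 13.7 points, instead of 10.

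Other readings of the start, end and cut-off dates give 36.5% to 45.7%. If the accrual rate rises linearly, the share is (10/24)² = 17%. The last woman has about 10 months of follow-up in December 2026 and completes 2 years in February 2028.

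**3. Effect on sensitivity.** Screen-detected cancers: 10 000 × 0.0092 = 92. Let k be the number of interval cancers and f the fraction MammoWave flags. The documents give neither; I assume k = 10, 20, 30 (1 to 3 per 1000) and f = 0.3 to 0.5. From an illustrative index sensitivity of 72/92 = 78.3%, the 2-year sensitivity is (72 + f·k)/(92 + k):

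| k | f = 0.3 | f = 0.5 |
|---|---|---|
| 10 | 75/102 = 73.5% | 77/102 = 75.5% |
| 20 | 78/112 = 69.6% | 82/112 = 73.2% |
| 30 | 81/122 = 66.4% | 87/122 = 71.3% |

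Five of the six cells are below 75%. The starting value matters. From 85% (78.2/92), the upper figure quoted for the algorithm in the section on its decision support system, the same grid gives 79.6/81.6%, 75.2/78.8% and 71.5/76.4%, so five of six stay above 75%.

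In general, the 2-year estimate exceeds 75% only if the index true positives exceed 69 + (0.75 − f)·k:
- k = 10, f = 0.5: 71.5, or 71.5/92 = 77.7%.
- k = 30, f = 0.3: 82.5, or 82.5/92 = 89.7%.

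**4. Effect on specificity.** Index non-cancers: 10 000 − 92 = 9908. At 90% specificity there are 8917.2 true negatives. Moving 30 interval cancers, half of them flagged, out of the non-cancers gives (8917.2 − 15)/(9908 − 30) = 90.12%, a change of about 0.1 point.

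**The case against.** The strongest reply is that the definitions need not be rivals. The abstract joins pathway and follow-up in one phrase, and the primary objective and the coding rule may simply be shortened. The Follow-up section also permits a staged reading, in which index labels come first and interval cancers are examined afterwards. This is a fair account of what may be intended. It does not say which stage supplies primary sensitivity and specificity, and the section with the operative coding rule has no follow-up element.

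The word "first" in the timeline, it can be added, implies a later evaluation, and data cut-offs belong in the full plan or the SAP. That stands: the article does not call the December 2026 evaluation final, so the dates alone are not a contradiction. But no later evaluation is named, and the December 2026 result is not described as provisional.

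Three stronger inferences should be resisted.

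- **The comparison with mammography is decided in advance.** A reader might infer this because a standard built on the index pathway favours mammography, and a secondary objective asks for "analysis of whether they are equivalent in terms of detection rates of BC (sensitivity"). The Follow-up section, however, assigns that comparison to the 2-year standard. Ultrasound for all 500 women of the preliminary phase, and after positive MammoWave labels later, can also bring cancers missed by mammography into the index standard.
- **Both primary estimates are materially affected.** Only sensitivity is, as step 4 shows.
- **Follow-up necessarily takes sensitivity below the target.** It depends on the starting value and on f. If MammoWave flagged interval cancers as often as screen-detected ones, sensitivity would not change.

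**Conclusion.** The inconsistency is real and concerns the primary endpoint. The primary objective and coding rule use the index pathway, while the abstract, the strengths and limitations box and the Follow-up section include 2-year follow-up. A woman with an interval cancer changes category between them.

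For sensitivity the difference can be several points: from 78% to about 66% to 75.5% in the illustration. This rests on assumed interval-cancer and flag rates and on point estimates. Whether the 75% target is met may therefore depend on the definition, but the documents do not show that it will.

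The February 2028 date for the last woman is plain arithmetic from the stated dates. The 42% to 46% share in December 2026 rests on even accrual, and would exceed half only if recruitment were front-loaded. The article does not suggest that: the Polish approval (March 2024) and the Swiss approval (June 2024) came after recruitment began.

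**What to change.** 1. Amend Hypothesis and objectives and Choice of comparator/control intervention to match the abstract, the strengths and limitations box and the Follow-up section. Positive means histologically confirmed cancer at index work-up or within 2 years; negative means no cancer through 2 years.
2. Correct the wording in Follow-up that calls a flagged interval cancer a false positive.
3. Label the December 2026 read-out as preliminary index-round (screen-detected) accuracy.
4. Base any claim of sensitivity above 75% and specificity above 90% against the 2-year standard, and the comparison with mammography, on completed follow-up.

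The cost is protocol and SAP wording, plus a later claim against the 2-year standard (February 2028 or after on the current timeline). The follow-up is already planned and the December 2026 read-out remains.

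If the sponsor intends an index-round primary endpoint, which the sample size would fit, that is an acceptable alternative. The abstract and the strengths and limitations box must then say so, and 2-year accuracy must be reported separately. Either way, the choice should be recorded before any accuracy results are seen.

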#### Study’s ethical conduct

The study will be carried out following the protocol and with principles enunciated in the current version of the Declaration of Helsinki, the guidelines of Good Clinical Practice issued by the International Council for Harmonisation of Technical Requirements for Pharmaceuticals for Human Use, in case of medical devices: the European Directive on medical devices 93/42/EEC and the ISO Norm 14 155 and ISO 14971, the European Law and the corresponding regulatory Competent Authorities requirements.

#### Patient privacy and confidentiality

The investigators will affirm and uphold the principle of the participant’s right to privacy. Especially, the anonymity of the participants will be guaranteed when presenting the data at scientific meetings or publishing them in scientific journals.

#### Patient and public involvement

This study will be carried out with patient involvement. Specifically, patient advocates and patient associations have been involved in the development of the study design, informed consent and satisfaction questionnaire. For example, within the development of the study design, patient advocates and patient associations highlighted the importance of EUSOBI recommendations for screening in dense breasts. This involvement has been possible since (a) one patient association, Evita Cancro (Portugal), is a partner of the project MammoScreen, (b) the MammoScreen project governance includes a dedicated patient advisory group (PAG), an external board comprising representatives from major national/European patient organisations. PAG is periodically invited to support MammoScreen and provide guidance on clinical protocol, patients’ continuous engagement tools, dissemination and communication strategy.

### Analysis

#### Number of participants

The maximum number of participants will be 10 000 (for all the sites). The sample size was determined using the Buderer approach,^40^ considering that (1) the primary objective of the study is to confirm that MammoWave reaches sensitivity >75% and specificity >90% in BC detection on 10 000 volunteers undergoing breast screening, (2) a two-tailed 95% CI for sensitivity and specificity (CI width=10) and (3) a prevalence of female BC detected due to screening of 0.92%, according to the official English statistics of the National Health Service (NHS) Breast Screening Programme.^41^ A minimum of 8000 participants is required to reach the primary endpoint.

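### The 8000-participant minimum gives sensitivity to about ±10 points (a 95% CI about 20 points wide), not the stated CI width of 10

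*Protocol article*

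**What the plan says.** All the relevant figures are in the protocol article, Analysis, Number of participants.

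- Method: "The sample size was determined using the Buderer approach".
- Aim that sets the planning values: to "confirm that MammoWave reaches sensitivity >75% and specificity >90% in BC detection".
- Precision: "a two-tailed 95% CI for sensitivity and specificity (CI width=10"). No unit is given, and nothing says whether this is the full width or the distance from the estimate to a limit.
- Prevalence: "a prevalence of female BC detected due to screening of 0.92"%.
- Result: "A minimum of 8000 participants is required to reach the primary endpoint".
- Ceiling: "The maximum number of participants will be 10 000 (for all the sites").

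No other section of the article restates or qualifies the precision. Statistical considerations leaves the analysis methods to the SAP, but the sample-size basis is stated in full here.

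**The concern.** Buderer's formula takes as its precision term the distance from the estimate to a confidence limit, which is half the interval. The article calls the 10 a width, which normally means the whole interval. The required number of cancers varies with the inverse square of this term, so the two readings differ fourfold in sample size and twofold in precision.

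This is the only precision statement for sensitivity, one of the two primary outcomes. A reader who takes it literally expects an observed 75% to carry limits of about 70% and 80%. With 8000 women the limits would be about 65% and 85%.

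The difference affects how the aim of exceeding 75% is judged. Suppose, as an assumption because the article does not define it, that confirmation means a lower 95% limit above 75%. A literal width of 10 suggests that an observed sensitivity of about 80% would be enough (75 + 5). With about 74 cancers, the observed figure would have to be about 84% (62/74, Wald interval) or 86% (64/74, exact interval). The section on the AI-powered decision support system reports a sensitivity of up to about 85% for the algorithm, so the requirement is close to the best performance reported.

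**Working it through.** **Inputs** (all from Number of participants): sensitivity Se = 0.75; specificity Sp = 0.90; two-sided 95%, z = 1.96; prevalence P = 0.0092; precision term 10, read as 10 percentage points; N = 8000 minimum, 10 000 maximum. Cancers are counted per woman.

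**Formula** (W = distance from estimate to limit):

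- cancers needed = z² × Se × (1 − Se) / W²
- women needed = cancers needed / P

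**Step 1. Reproduce the 8000, with 10 points as the half-width (W = 0.10).**

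- 1.96² × 0.75 × 0.25 / 0.10² = 72.0 cancers
- 72.03 / 0.0092 = 7829 women (7935 if cancers are first rounded up to 73)

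Both are within 3% of 8000.

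**Step 2. Take 10 points as the full width (W = 0.05).**

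- 1.96² × 0.75 × 0.25 / 0.05² = 288.1 cancers
- 288.1 / 0.0092 = 31,316 women (31,414 if rounded up to 289 cancers)

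This is about four times the stated minimum and three times the maximum.

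**Step 3. Try other planning values.**

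| Variant | N, half-width 10 | N, full width 10 |
|---|---|---|
| Se 0.75, two-sided | 7829 | 31,316 |
| Se 0.75, one-sided z | 5514 | 22,056 |
| Se 0.80, two-sided | 6681 | 26,723 |
| Se 0.85, two-sided | 5324 | 21,295 |

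Only the first row under half-width matches 8000. Every full-width variant exceeds 21,000.

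**Step 4. Precision for sensitivity at the stated sizes (Se = 0.75).**

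- 8000 women: 8000 × 0.0092 = 73.6 cancers; half-width 1.96 × √(0.1875 / 73.6) = 0.0989; full width 19.8 points.
- 10 000 women: 10 000 × 0.0092 = 92 cancers; half-width 1.96 × √(0.1875 / 92) = 0.0885; full width 17.7 points.

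The interval method makes little difference. For 56 of 74 cancers detected, the exact (Clopper-Pearson) interval is 64.3% to 84.9%, a width of 20.6 points, and the Wilson width is 19.2 points.

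**Step 5. Specificity.**

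- W = 0.10: 1.96² × 0.90 × 0.10 / 0.10² = 34.6 women without cancer; / 0.9908 = about 35 women.
- W = 0.05: 138.3; / 0.9908 = about 140 women.
- With 8000 women the full width is about 1.3 points.

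Specificity does not determine N and is estimated far more precisely than either reading of the 10 requires.

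**Step 6. What would make a 10-point full width true?** With 73.6 cancers, sensitivity would have to be about 95%; with 92 cancers, about 94%. Alternatively, at Se = 0.75, 8000 women would have to yield 289 cancers, a prevalence of 289 / 8000 = 3.6%.

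**The case against.** The strongest reply is that 8000 is correct and only a word is loose. The article names Buderer's method, whose precision term is a half-width, and the inputs return about 8000 when the 10 is used in that way. A statistician can work out the intended meaning, and N, the outcomes, the analysis sets and the interim rule are all unaffected. This stands as an account of how the wording probably arose. It does not make the sentence right: nothing printed says half-width, margin or ±, so a reader has to solve the formula backwards to learn the precision.

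A second reply is that 18 to 20 points is not a fixed outcome. At Se = 0.85 the width would be about 16.3 points with 8000 women and 14.6 with 10 000, and interval cancers found during the 2-year follow-up would add cases. This also stands, and the width should be given with the sensitivity it assumes. Neither effect brings the width near 10.

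Third, the article condenses a clinical investigation plan that is not shown and that may word the precision properly. That cannot be checked and is a reason to look there too. The article itself still prints inputs, precision and N that do not fit together.

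Finally, the sponsor may have meant a full width of 10. The derivation makes that unlikely. If it was meant, N is about four times too small, and the half-width statement would still describe what this design can deliver.

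**Conclusion.** The concern holds. In the ordinary sense of the term, a 95% CI width of 10 points for sensitivity is not delivered by 8000 women (19.8 points) or by 10 000 (17.7 points), so the stated precision is too favourable by a factor of about two. The minimum of 8000 follows correctly from a half-width of 10 points; the error is in the label, not in the sample size. Specificity is unaffected.

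The widths assume a sensitivity of 75%, the document's prevalence of 0.92%, one cancer count per woman, and a Wald interval. They depend directly on prevalence: if it were 0.6% (an assumption for illustration), 10 000 women would give 60 cancers and 1.96 × √(0.1875 / 60) = 0.110, or ±11 points. The contradiction between a width of 10 and a minimum of 8000 does not depend on that scenario.

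**What to change.** In Number of participants, replace the width statement with a half-width of 10 percentage points (total width about 20) for sensitivity. Beside it, give the expected precision at a sensitivity of 75% and prevalence of 0.92%:

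- 8000 women: about 74 cancers, ±9.9 points.
- 10 000 women: about 92 cancers, ±8.8 points.

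Say that sensitivity alone determines the sample size. The sponsor should confirm that a half-width was intended, and carry the same wording into the clinical investigation plan and the SAP wherever they repeat the figure.

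The cost is a change of wording only. No additional women are needed, and the outcomes, analysis sets and interim rule stay as they are. The stated precision becomes less favourable, but it will match what the trial can deliver.

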#### MammoWave’s AI-powered clinical decision support system

MammoWave’s novel software includes an AI (machine learning-based) classification algorithm. This algorithm has been developed using the clinical data collected in a previous international, multicentric study (ClinicalTrials.gov Identifier: NCT04253366). In particular, the labels (reference standard, ie, the output of conventional breast examination path) collected in such study were used for training and testing, with the aim of optimising the AI-based classification algorithm (to be used, prospectively, within this clinical trial).

This AI-based classification algorithm works on the S_21_ data of each scanned breast, which is a matrix of complex electromagnetic signals derived from the measurement performed for multiple positions of the TX and RX antennas and sampled in frequency. Principal component analysis methods were used to reduce the matrix’s dimensionality and fix the number of components so that at least 95% of the variance in the data is accounted for. Various algorithms were tested (support vector machines (SVM), decision trees, random forests, logistic regression, k-nearest neighbours), using the cross-validation methodology and calculating the performances in terms of specificity and sensitivity.^36^ More specifically, the SVM-based algorithm will be used within this trial to categorise breasts into two groups: WSF (breast With Suspicious Finding), indicating the presence of a suspicious lesion, or NSF (No Suspicious Finding), indicating the absence of a lesion or the presence of a low-suspicion lesion. More details related to algorithm’s validation methodology and performances in terms of specificity and sensitivity can be found in Papini *et al*,^36^ where specificity of up to ~90% and sensitivity of up to ~85% have been reported.

As an example, figure 2 shows MammoWave’s output and reference standard output is also shown.

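### The minimum of 8000 women is a precision figure (about ±10 points on sensitivity); it does not establish power to confirm sensitivity above 75% or specificity above 90%

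*Protocol article*

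**What the plan says.** Under Hypothesis and objectives, the article's hypothesis is that the algorithm "achieves a sensitivity of over 75% and a specificity of over 90% in the detection of BC". Number of participants repeats this as the basis of the size: "the primary objective of the study is to confirm that MammoWave reaches sensitivity >75% and specificity >90% in BC detection".

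The method follows in the same section: "The sample size was determined using the Buderer approach", with a "two-tailed 95% CI for sensitivity and specificity (CI width=10" and "a prevalence of female BC detected due to screening of 0.92" per cent. It concludes: "A minimum of 8000 participants is required to reach the primary endpoint". The maximum is 10 000. The section gives no expected sensitivity or specificity other than the thresholds, and no power.

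On earlier performance, the section on the AI-powered decision support system says: "specificity of up to ~90% and sensitivity of up to ~85% have been reported".

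The only decision metric in the article is the interim rule under Statistical considerations. It compares the lower limit of the 95% CI with 60% for sensitivity and 70% for specificity.

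**The concern.** Estimating a proportion to a given precision and showing that it exceeds a threshold are different tasks. The Buderer formula does the first. For the second, the size depends on how far the true value is expected to lie above the threshold, and the section states no such distance. Tying 8000 to reaching the primary endpoint therefore credits the number with a property that the calculation does not give it.

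The primary conclusion is at stake. A sensitivity of 75/92 (81.5%), for example, lies above 75% as a point estimate, but its lower 95% limit does not. A reader told that 8000 women are what the endpoint requires would not expect that outcome, although it is quite likely at plausible true sensitivities.

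**Working it through.** **Inputs.** From Number of participants: thresholds 75% and 90%, two-sided 95% confidence, width 10, prevalence 0.92%, N = 8000 and 10 000. From the AI section: reported sensitivity up to about 85% and specificity up to about 90%. Assumptions made here: the true accuracy values below, one unit per woman, and cancers counted at 0.92%.

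**Step 1: reproduce 8000.** N = z² × Se(1 − Se) / (d² × prevalence).

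- Se = 0.75, d = 0.10: 3.8415 × 0.1875 / 0.01 = 72.03 cancers; 72.03 / 0.0092 = 7829 women (7935 if rounded up to 73 cancers). This is close to 8000.
- Same d, other sensitivities: 0.70 gives 8769, 0.80 gives 6681, 0.85 gives 5324, 0.90 gives 3758.
- Se = 0.75, d = 0.05 (full width 10): 288.11 / 0.0092 = about 31 300 women.
- Specificity 0.90 needs only 35 women (d = 0.10) or 140 (d = 0.05), so sensitivity drives the size.

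The number thus fits a half-width of 10 points around 75%.

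**Step 2: precision delivered at sensitivity 75%.** Cancers: 8000 × 0.0092 = about 74; 10 000 × 0.0092 = 92. Half-widths: 1.96 × √(0.1875/74) = 9.9 points; 1.96 × √(0.1875/92) = 8.8 points.

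**Step 3: power for sensitivity.** Success is defined as a lower two-sided 95% limit above 75%. For each interval method, find the smallest number detected that succeeds, then take the exact binomial probability of reaching it.

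| Women (cancers) | Interval | Detected needed | True 80% | True 85% | True 90% |
|---|---|---|---|---|---|
| 8000 (74) | Clopper-Pearson | 64 (86.5%) | 10% | 44% | 88% |
| 8000 (74) | Wilson | 63 (85.1%) | 17% | 57% | 94% |
| 8000 (74) | Wald | 62 (83.8%) | 26% | 69% | 97% |
| 10 000 (92) | Clopper-Pearson or Wilson | 78 (84.8%) | 15% | 59% | 96% |
| 10 000 (92) | Wald | 77 (83.7%) | 23% | 70% | 98% |

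**Step 4: power for specificity, per woman.** Success is a lower 95% limit above 90%; Clopper-Pearson and Wilson agree.

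| Women (non-cancers) | Correct needed | True 90% | True 90.5% | True 91% |
|---|---|---|---|---|
| 8000 (7926) | 7186 (90.7%) | 2.5% | 32% | 86% |
| 10 000 (9908) | 8976 (90.6%) | 2.5% | 38% | 92% |

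**Step 5: what a power-based size would depend on.** For 80% power with the Clopper-Pearson limit, true sensitivity 90% needs about 59 cancers (about 6400 women) and true 85% about 142 cancers (about 15 400 women). So 8000 is not a general minimum for confirmation: it is more than needed at 90% and too few at 85%. These sizes only illustrate the point; none is proposed.

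**The case against.** Several points on the other side have weight.

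- **The planning value is inferred.** The article does not say that 75% was entered. A sensitivity of 74% gives 8034 women, and 80% with an assumed 20% allowance gives 6681 × 1.2 = 8017. The 75% input is the most natural reading because it is the only sensitivity the section supplies, but it is not proven. The point does not depend on it, since no input gives the formula a power term.
- **The sentence states a floor, and the plan recruits up to 10 000.** True, but step 5 shows that 8000 is not a floor for confirmation either.
- **Sizing a single-arm accuracy study on precision is a recognised choice.** That stands. The fault is in describing the result as what the confirmatory endpoint requires.
- **The final success rule may be in the SAP.** It may, and its absence from an article is not the complaint. A rule in the SAP would not turn the precision calculation into a power calculation.
- **Counts and units may differ.** Two-year follow-up can add interval cancers. Labels are per breast; ignoring clustering, specificity power per breast at 10 000 women and true 90.5% would be about 65% instead of 38%.

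A reader might infer that confirmation is almost impossible, because at a true sensitivity of exactly 75% the chance is about 1–5%. The documents do not support that. A planning value in a precision formula sets the variance and does not predict performance, and a success chance near the error rate at the threshold holds for any N.

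A reader might also multiply 59% by 2.5% and conclude that joint power is 1.5%. That treats an approximate development figure as an exact true specificity of 90.0%, although Study design plans a 500-woman phase to fine-tune the algorithm.

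**Conclusion.** The point holds as a mismatch between the stated purpose and the calculation, and it should be fixed. About 8000 women support estimating sensitivity to roughly ±10 points. They do not establish power to show that it exceeds 75%. On a lower-limit criterion, power at the best reported sensitivity (about 85%) is 44–69% with 8000 women and 59–70% with 10 000; at a true 90% it is high at either size. Specificity needs a true value about one point above its threshold, while the best development value sits approximately on it.

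The figures assume one unit per woman, cancers at 0.92%, and confirmation judged by the lower two-sided 95% limit. That criterion is consistent with the two-tailed interval in the sizing and with the interim rule, but the article does not state it for the final analysis. Separately, the stated CI width of 10 reproduces 8000 only as a half-width.

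**What to change.** In Number of participants (and in the SAP where it repeats the sizing):

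1. Replace the sentence on the 8000 minimum with a statement that about 8000 women, with about 74 cancers expected, give a 95% CI half-width of about 10 points for sensitivity.
2. Correct the CI width of 10 to a half-width of 10 percentage points, and state the sensitivity used in the formula.
3. Report power at 8000 and 10 000 over a range of true sensitivity and specificity, as in the tables above, naming the interval method and the unit of analysis (woman or breast).
4. Speak of confirming the hypothesis only if both lower 95% limits, computed on the actual counts, exceed 75% and 90%. This matches the metric of the interim rule. Otherwise report the results as estimates with their intervals.

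The cost is wording only, with no extra enrolment. The downside is a less favourable stated chance of success. The change should be made before the first evaluation of results, planned for December 2026.
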